### **1.2.7. Blood biomarkers**

Beyond neuropsychological and neuroimaging markers, blood-based biomarkers are the subject of intense research because of the accessibility advantages of a blood test. The study of meditators via biochemical and hormonal assays has revealed a number of neurochemical, hormonal and epigenetic changes. Changes in plasma serotonin and cortisol, correlated with neurophysiological changes, have been observed and are thought to follow the frontal activation related to the attentional mobilization required by meditation techniques (Newberg & Iversen, 2003; Yu et al., 2011). Hormonal changes are also numerous: modification of the corticotropic axis, decrease in TSH... (Elias & Wilson, 1995). The effects of meditation on the immune system have highlighted its down-regulatory role via the hormonal pathway mainly (release of CRF, decrease in cortisol...) (Downing & Miyan, 2000) but also via the brain effects of cytokines (Pace et al., 2009; Rosenkranz et al. 2016). Finally a meditative practice would contribute to increase the activity of telomerases, responsible for telomere length which is a predictor of immune cell longevity (Jacobs et al., 2011; Kaliman et al., 2014). This still recent field of inquiry has paid very little attention to the influence of meditative expertise on a large number of biological markers that we wish to study in this protocol. Measurements of i) general health such as blood count, urea, creatinine, gamma-glutamyl transferase, aspartate aminotransferase and alanine

aminotransferase, glycemia, insulin and fibrinogen, triglyceride-cholesterol, HDL and LDL, bioavailable testosterone, estradiol and Sex Hormone Binding Globulin (SHBG), Dehydroepiandrosterone-Sulfate (SDHEA), Thyroid Stimulating Hormone (TSH) and Brain Natriuretic Protein (BNP), ii) stress and inflammation such as ultra-sensitive C Reactive Protein (CRP), cytokines, cortisol, insulin growth factor 1 (IGF-1), peroxyredoxin, iii) aging and dementia (AD) such as telomere length, telomerase activity, lymphocyte senescence (exploration of cellular immunity via B, T, and NK cells), Brain-Derived Neurotrophic Factor (BDNF), GWAS genotyping (specifically APOE), A $\beta$  1-40 and 1-42, Tau/phosphoTau proteins, tPA and PAI-1, expression of proteins of interest (REST) (Lu et al. , 2014), neurofilament light (NFL) (Zhou et al., 2017) and glial fibrillary acidic protein (GFAP) and iv) mood such as serotonin will allow us on the one hand **to characterize the health status of the participants and, on the other hand to determine the specific biological signatures of an 18-month meditative practice (intervention with non-meditating seniors) and of a long-term meditation practice (with the meditating expert population). A sample will be taken at the beginning of the trial, another at the end of the trial and another one after 35 months after the end of the intervention. We will thus be able to identify whether these biological markers can be modulated by this type of mental training and to trial these parameters in relation to cognitive changes occurring during normal aging.**

### 1.2.8. Effect of gender

Dementia in general and AD in particular are more common in women than in men because women may have a greater susceptibility to develop the disease (Alzheimer's Association 2014). Beyond AD, studies suggest that the processes involved in so-called "normal" aging differ between men and women (Gur and Gur 2002; Chêne et al. 2015). Recent reviews have emphasized the importance of investigating these specificities in more detail to better understand the mechanisms and develop the most appropriate treatments (Rocca et al., 2014). The origin of these differences is poorly understood. They could reflect intrinsic sex differences (genetically and/or hormonally related) (Gillies and McArthur, 2010), and/or lifestyle differences related to the socio-cultural context - inducing different exposure to dementia risk factors such as smoking (Ford et al., 2004), alcohol (French et al., 2014), diet, (Larrieu et al., 2004) depression (Djernes, 2006), or even educational level (Jack et al., 2015) or occupation (Valenzuela et al., 2013). On the other hand, recent evidence suggests that meditation-based interventions may benefit women more than men (de Vibe et al., 2013). In this trial, we will therefore focus on the effect of gender on AD risk factors, the mechanisms involved in aging and Alzheimer's disease, and the impact of meditation.

### 1.2.9. Electrophysiological markers of activation and rest by electroencephalography (EEG)

An evoked potential refers to the change in electrical potential produced by the nervous system in response to an external stimulation, particularly sensory (i.e. sound) recorded using techniques such as electroencephalography (EEG). EEG is a non-invasive brain imaging technique that does not involve

the injection of contrast media. No risk has been identified for this method. Evoked potentials are used in human neurophysiology to understand the functional organization of the nervous system. The MMN (mismatch negativity) is a component of the evoked potential generated mainly by the auditory cortex obtained by an oddball paradigm. The oddball paradigm consists of presenting a deviant or rare stimulus during the presentation of series of repeated stimuli with the same physical characteristics. The MMN is obtained by subtracting the EEG waves corresponding to the repeated stimuli from those of the deviant stimuli. The MMN is generated by any discriminable sound change in a repetitive stimulation environment. The amplitude of the MMN is lower and its latency longer in older adults indicating a deterioration and slowing down of the automatic detection of changes (NDDIN ZOTERO\_ITEM CSL). MMN may also be used as a marker of cognitive decline and Alzheimer's disease (Ruzzoli et al. 2016). MMN occurs largely automatically, regardless of the subject's attentional focus, although recent studies have shown that it is modifiable by attentional states such as meditation (Biedermann et al. 2016). **The use of this evoked potential thus appears to be a judicious electrophysiological marker to measure functional modifications related to aging and to explore the effect of aging, both at the cognitive and cerebral levels, following a sustained meditation practice in an older adults population.**

Before measuring MMN, we would like to record spontaneous EEG activity during a resting state for ten minutes. Resting state EEG allows the identification of rhythmic brain electrical activities that are classified according to their frequency. Analysis of the spectral power of these rhythmic activities, and of the functional connectivity of the oscillatory activity to these rhythms, allows us to characterize dynamic markers of psychological states such as meditative states or pathological states, like Alzheimer's disease. For example, we have recently shown that one-day meditation training increases the activity of theta (3-8Hz), alpha (8-13Hz) and beta (13-25Hz) rhythms over frontal and parietal electrodes. In contrast, many studies have linked Alzheimer's disease to a decrease in these rhythms and an increase in slow waves in the slow frequencies (delta 1-4Hz) (Babiloni et al. 2016). Long-range connectivity between fronto-parietal, or frontotemporal EEG electrodes are also abnormal in subjects with Alzheimer's (Babiloni et al. 2016). **The study of the resting EEG neurodynamic profile will be relevant not only to assess the effects of meditation in normal and pathological aging but also to try to better understand the mechanisms underlying these effects.**

## 2. OBJECTIVES

This research aims to **determine the effects of an 18-month meditation practice on imaging, biological, and behavioural markers** particularly associated with aging and AD and **to better understand the cognitive and emotional mechanisms** underlying these effects. All the objectives and corresponding analyses are detailed below.

We hypothesize that an 18-month meditation intervention will result in an increase in volume and/or perfusion of the anterior cingulate cortex. This intervention will be compared to a passive control (participants receiving no intervention in the trial). We also hypothesize that an 18-month meditation intervention will result in increased volume and/or perfusion of the insula compared to a foreign language

learning intervention, designed to have a similar structure to the meditation intervention. The non-specific effect of meditation on the anterior cingulate cortex will be estimated by comparing it to the passive control group. The specific effect of meditation on the insula will be estimated by comparing it to the foreign language learning group.

## **2.1. Main objectives**

The **main objectives** of the trial are:

- To estimate the effect of an 18-month meditation intervention in non-meditating senior participants on volume and perfusion of the anterior cingulate cortex compared to a passive control (**OBJECTIVE 1**);
- To estimate the effect of an 18-month meditation intervention in non-meditating senior participants on the volume and perfusion of the insula compared to an 18-month foreign language learning intervention (**OBJECTIVE 1bis**).

## **2.2. Secondary objectives**

### **2.2.1. Secondary objectives in relation to the interventions**

**OBJECTIVE 2:** To compare the effects of the two interventions (meditation and foreign language learning, for 18 months) with each other and with a passive control in non-meditating seniors, on behavioural and biological measurements (cognitive, psycho-affective, blood, sleep, and imaging), including measurements to assess potential deleterious effects as well as gender-specific effects (men/women);

**OBJECTIVE 2 bis:** To estimate the maintenance of the effect of the interventions (meditation and foreign language learning) in the long term (29 months after the end of the intervention) on cognition, psycho-emotional factors, sleep, and lifestyle (and imaging and blood markers if the budget allows).

**OBJECTIVE 2 ter:** To compare the long-term effects (29 months after the end of the intervention) of the 2 interventions (meditation and foreign language learning) with each other on cognition, psycho-emotional factors, sleep, and lifestyle (and imaging and blood markers if the budget allows).

**OBJECTIVE 3:** To estimate the effect of the interventions (meditation and foreign language learning, for 18 months) on the volunteers' entourage (i.e., their perception of the volunteers' changes, their interaction with the volunteer, and their willingness to help the volunteer), compared to a passive control.

**OBJECTIVE 3 bis:** To compare the long-term effects of the interventions (meditation and foreign language learning) on the volunteers' entourage (i.e., their perception of the volunteers'

changes, their interaction with the volunteer, and their willingness to help the volunteer) 29 months after the intervention ended.

**OBJECTIVE 3 ter:** To estimate the effect of the interventions (meditation and foreign language learning, for 18 months) (i.e. their acceptance of the intervention, their perception of the changes...).

**OBJECTIVE 3 quater:** To assess the consistency between participants' perceptions of the interventions and their effects and those of the meditation or English teachers (after the interventions have ended).

### 2.2.2. **More exploratory secondary objectives (not related to the interventions)**

**OBJECTIVE 4:** To estimate the association between meditation expertise and behavioural and biological measurements (cognitive, psycho-affective, life factors, blood, sleep, and imaging), comparing expert meditators and non-meditating seniors;

**OBJECTIVE 5:** To identify, in senior meditation experts, the neural signatures of two meditative practices (mindfulness meditation and compassionate meditation), i.e. the specific neural activity associated with each practice;

**OBJECTIVE 6:** Explore associations between lifestyle factors (cognitive activity, diet, and physical activity), psycho-emotional measurements, and behavioural and biological measurements (cognitive, psycho-emotional, lifestyle factors, blood, sleep, and imaging), as well as gender-specific associations (male/female);

**OBJECTIVE 7:** To explore the pathophysiological mechanisms of AD by studying the links between different measurements as well as the influence of structural and functional connectivity on the spread of lesions, as well as gender-specific effects (male/female);

**OBJECTIVE 8:** To compare the early FDG-PET perfusion measure to the early Amyvid®-PET perfusion measure to better understand the relationships (and potential changes in coupling) between metabolism and perfusion and compare the sensitivity of the two measurements to assess the effects of interventions;

**OBJECTIVE 9:** To identify determinants of well-being and mental health in aging in volunteers and their designated partners from cognitive data, psycho-emotional, sleep, and lifestyle measurements (as well as imaging and blood markers if budget allows) in passive control participants.

The list of exploratory analyses may be updated according to the progress of knowledge in the field or the results of the primary or secondary objectives. The scientific rationale will be presented to the Scientific Council.

### 3. TRIAL TYPOLOGY AND EXPERIMENTAL DESIGN

#### 3.1. Trial type

Biomedical research with health product, monocentric, studying two participant populations (expert meditators and non-expert seniors):

1) Monocentered, randomized, controlled trial with blinded assessment of achieved measurements, with three parallel arms comparing an 18-month meditation intervention, an 18-month foreign language learning intervention, and a no-intervention group, in volunteer participants over 65 years of age with no meditative practice experience (non-meditative seniors).

2) Cross-sectional study evaluating the association between meditation practice and health status markers, including consecutively meditating experts in order to compare their characteristics with those of non-meditating seniors at inclusion in the randomized trial.

This trial is classified as non-health product despite the use of Amyvid® and/or FDG in PET imaging scans performed at inclusion (Visit 1 and for meditating experts), 18-month follow-up (Visit 3) and long-term follow-up (35 months post-intervention) of all participants.

#### 3.2. Statement of the experimental design

[figure not shown]

Figure 2: Experimental design of the Age-Well trial

Four groups will be made:

| Expert Meditators    | Non-expert seniors                  |                                          |                                 |
|----------------------|-------------------------------------|------------------------------------------|---------------------------------|
|                      | Meditation Group                    | Foreign Language Learning Group          | Passive Control Group           |
| 30 expert meditators | 50 seniors with 18-month meditation | 50 seniors with 18-month english lessons | 50 seniors with no intervention |

Tableau 1: Study groups

### Methods for randomization:

The randomization list will be established by the biostatistician of the Centre de méthodologie et de gestion (EUCLID, CHU Bordeaux, France and Inserm, F-CRIN platform) before the beginning of the research. The allocation of the intervention will be done according to a 1:1:1 ratio.

- Group 1: Meditation
- Group 2: Learning a foreign language (English)
- Group 3: Passive control (follow-up without intervention)

A document describing the randomization procedure will be kept confidential by the EUCLID Statistician. The randomization of the participants will be done before the beginning of the intervention by the investigator in a centralized way via the Ennov Clinical software. This centralization allows the investigator and possibly other correspondents to be informed of the randomization of each participant. From the second wave onwards, the foreign language learning group will be divided into 2 subgroups in order to respect the logistic constraints on group size. The allocation in each of the two English groups will be drawn at random, and adapted by the English teachers if necessary from the level assessed during the English test carried out during the diagnostic battery, to limit the heterogeneity of level within the same group.

Assignment of the non-medical senior intervention is unbeknownst to the individuals responsible for data analysis for all visits, including visit 4.

The investigating team (medical investigators, neuropsychologists, radiological manipulators, nuclear physicians) knowing the identity of the participants is not the one who analyses the data.

### Interventions:

The content of the different interventions is described in section 6.9.

## 3.3. Provisional schedule of the trial (Flow-Chart)

The projected schedule for the trial is illustrated in Figure 3 below:

Duration of recruitment:

- Non-expert seniors: recruitment will take place 3 months before the beginning of each inclusion wave, i.e. 9 months of recruitment.
- Expert meditators: recruitment will be done on an ongoing basis and over a total period of 73 months (until February 2022; due to an interruption in recruitment in 2020 and part of 2021 linked to COVID-19 and the resulting health measures).

Maximum duration of participation for each participant:

- Expert meditators: 6 months (Screening visit V0 + Inclusion visit V1)

And in the Age-Well substudy - Lockdown: 24 months (April 2020-April 2022)

- Non-expert seniors: 53±6 months (3 months for V0 + V1 + 18 months for intervention + 3 months for Follow-up Visit 3 + 29 months without intervention which is the long-term post-intervention visit (V4)) (± 6 months depending on health status changes and a possible new period of confinement). Total duration of data collection: 6 years (1st participant included in December 2016 and last follow-up of the last participant: in June 2022 ± 6 months depending on the evolution of the health situation and a possible new containment period).

And in the Age-Well substudy - Lockdown: 24 months (April 2020 - April 2022)

Total duration of the research: 7 years (6 years for data collection + 1 year for data analysis) as shown below:

[figure not shown]

Figure 3: Provisional schedule of the Age-Well trial (data collection and analysis).

## 4. SELECTION OF PARTICIPANTS

### 4.1. Study populations

| Group                     | Description of the participants                                                                                      | Number to be included     | Duration of participation in the trial |
|---------------------------|----------------------------------------------------------------------------------------------------------------------|---------------------------|----------------------------------------|
| Expert meditators  | Independent and willing people over 65 years old with a regular practice of mindfulness and compassionate meditation | 30                        | 6 months                               |
| Non-expert seniors | Independent and willing people over 65 with no previous meditation experience                                        | 150 (included in 3 waves) | 53 ± 6 months                          |

Tableau 2: Study Populations

### 4.2. Eligibility criteria

Eligibility criteria will be verified during the recruitment phase, which includes an inclusion visit with the investigating physician and psychologist. The investigator will be responsible for providing all the necessary information and collecting the signed consent of the participant before any procedure is performed. After this interview, the inclusion of the participants will continue with a psychologist who will conduct an interview and tests.

Monitoring of eligibility criteria will take place over a maximum period of 3 months after consent is signed. It is assumed that the set of measurements performed within this time frame reflects a steady state characterizing the participant's condition at inclusion.

#### 4.2.1. Inclusion criteria

**For all the participants:**

- Age  $\geq$  65 years old;
- Be independent (assessed by the following question asked by the physician during an interview with the participant, and their partner when present: would you be able to live on your own, on a purely "functional" and not emotional level?);
- Living at home;
- Have a level of education  $\geq$  7 years (from the 1st grade included);
- Be a member or beneficiary of a social security regime;
- Be motivated to participate effectively in the project and sign the informed consent of the protocol in agreement with the Comité de Protection des Personnes;

- Present normal neuropsychological performance (based on age, gender, and education level) on the diagnostic battery tests (Table 4, Section 6.4).

**Specific criteria for non-experts seniors:**

- Be a native French speaker;
- Be available for at least the next 24 months (this criterion will be verified during the individual interviews or the question of availability for the next 24 months may be explored);
- Retired from the profession for at least 1 year;
- Have no strong preference nor objection to any of the three intervention groups (assessed by a question to the participant);
- Not have practiced meditation or comparable practices (yoga, Qi Gong, Alexander Technique) regularly or intensively EITHER:
  - > 1 time per week for 6 or more months in a row in the past 10 years,
  - intensively (internship or retreat > 5 consecutive days) within the last 10 years,
  - > 25 days of retirement accumulated before the last 10 years;
- Not fluent in English (assessed by asking the participant, "Are you fluent in English, can you hold a conversation with ease?"; only those answering no to this question will be included in the trial).

**Specific criteria for the expert meditators:**

- At least 10,000 hours of formal meditation practice in a lifetime, including at least 6 months in retreat;
- Have a daily meditation practice (at least 6 days/week, at least 45 minutes per day on average; Practice mindfulness meditation (i.e. mindfulness, Samatha/ Vipassana, Zazen (Zen), Shikantaza (Zen), focused attention, Mahamudra/ Dzogchen), and compassionate/ loving-kindness meditation (i.e. tonglen practice, "four immeasurable qualities" (metta/ karuna) practices, Bodhichitta meditation).

*These criteria will be assessed in a semi-structured interview including a detailed assessment of the type, duration and frequency of meditation during the lifetime.*

### **4.3. Recruitment method**

The meditating experts will be recruited in France and abroad under the responsibility of [name] (Research Fellow at the Research Center in Neurosciences, Lyon, France), who has experience in several neuroscience researches on meditating experts, with the help of [name] (Centre d'Etudes de Chanteloube, France), Expert-Associate. This recruitment will be done in meditation centers and monasteries of the Buddhist tradition. Participants will have to follow the criteria for inclusion in the trial as detailed below, and will have to be recommended by the meditation teachers of their center. These centers will be required to offer teachings and practices in mindfulness meditation techniques and compassionate and loving-kindness meditation. The recruitment process will be as follows. With the support of [name], who is an emblematic figure of Buddhism in France, we will contact teachers in charge of Buddhist meditation centers in France and in Europe to present our trial and our needs for the trial. These teachers will contact meditation practitioners.

The following centers and their affiliates will be contacted:

1) Centre de méditation de la tradition du Bouddhiste Tibétain dans la lignée Kagyu, la lignée Nyingmapa et la lignée Gelugpa.

- Monastère et centre de méditation Dhagpo Kundreul Ling: [name] (<http://www.dhagpo-kundreul.org/index.php/fr/>)

- Centre d'étude et de pratique du bouddhisme tibétain de Montchardon [name] (<http://www.montchardon.org/indexspip.php>)

- Association du Centre d'Etudes de Chanteloube: [name] (<http://chanteloube.pagesperso-orange.fr/chanteloube.htm>)

- Centre Rigpa de Lérab Ling [name] (<https://lerabling.org/lang-fr/>)

2) Centres de méditation du Bouddhiste Théravada:

- L'Association de Méditation Bouddhique – Centre Vimalakirti, [name] (<http://www.vimalakirti.org>)

- Centre Bouddhique International - Pagode du Bourget, [name] (<http://centrebouddhique.fr>)

3) Centres de Bouddhisme Zen Coréen, Vietnamien, ou Japonais:

- Village des Pruniers (Thich Nhất Hạnh), [name] (<http://villagedespruniers.net>)

The procedure for recruiting the non-expert seniors is shown in Figure 4. The non-expert seniors will be recruited in the Caen area through a communication campaign established by two communication companies: Minerva, located in London and specialized in the communication of European projects, and Mediapilote, located in Caen and responsible for its local implementation. This communication campaign will be aimed at the general public and at target institutions having a privileged link with the population of interest in this trial, i.e. people over 65 years old (the CLIC - Centres Locaux d'Information et de Coordination gérontologique, l'Espace 14, the Calvados Department, the Basse-Normandie Region, the Caen La Mer Community of Municipalities, etc.) The recruitment will be done through posters, and via various media. A conference and an online questionnaire (secure site) will allow to explain the trial to the participants and to verify their motivation as well as to check that the participants who will be invited to sign the consent form correspond to the target population (e.g. over 65 years old, retired for more than one year, etc). One of the investigating physicians will be present during the conferences explaining the protocol to potential future participants in order to answer any questions. The signature of the consent form will only be done at a second stage during the selection visit (V0 visit, see below) which will take place at least one week after the conference in order to give the participants time to reflect..

| RECRUTEMENT            |                            | VISITE DE SELECTION - V0  |                   |                                                                       |
|------------------------|----------------------------|---------------------------|-------------------|-----------------------------------------------------------------------|
| Campagne d'information | Conférence et présélection | Signature du Consentement | Entretien médical | Examens psychologiques (entretien et batterie de tests diagnostiques) |

Figure 4: Recruitment procedure

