This project is based on the premise **that mental training in stress and emotion regulation through meditation could reduce these effects and thus improve the well-being and mental health of seniors and delay AD or reduce the risk of AD**. Although research in this field is still recent, studies have shown encouraging effects in seniors. Notably, meditation is reported to be associated with improved cognitive abilities (mainly attention but also memory, which are the two most age-sensitive functions and the most frequently impaired in AD) (Gard et al., 2014; Marciniak et al., 2014; Newberg et al., 2014). Other studies have shown that meditation is also thought to be associated with reduced stress, anxiety, depression, insomnia, feelings of loneliness and social exclusion (Chen et al., 2012; Innes and Selfe, 2014), and cardiovascular risk (Schneider et al., 2012). Furthermore, related to the notion of neuroplasticity, neuroimaging studies have shown that meditation is not only associated with a change in brain activity pattern during practice but may also produce long-term structural and functional brain changes, particularly in frontal and limbic areas (Newberg et al., 2014; Slagter et al., 2011) (Fox et al., 2014; Marciniak et al., 2014; Tang et al., 2015) -known to be susceptible to aging and AD. Finally, recent studies have shown that meditation may increase telomerase activity that impacts aging and AD (Schutte and Malouff, 2014). However, these results need to be confirmed, strengthened, and refined; indeed, the populations studied are very heterogeneous, the size of the studies remains small, and very few studies include a comparison to another type of active intervention. In this trial, therefore, we propose to include an active intervention and to use a randomized allocation to control for potential selection and confounding biases in order to preserve the validity of the comparisons. We chose to use an active foreign language learning intervention (English) because 1) like meditation, this learning corresponds to mental training; 2) its organization can structurally resemble the meditation intervention (group sessions, daily practice with audio support, etc.); 3) a positive effect can be expected because foreign language learning is known to have a positive impact on cognitive functions and brain

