#### For participants without previous meditation practice

- French mother tongue;
- Available for the trial duration (24 months);
- Retired since 1 year or more;
- No preference regarding the intervention group;
- Not having regularly or intensively practiced meditation or comparable practices (yoga, Qi Gong, Alexander technique)
  - more than one day per week for more than six months consecutively over the last 10 years,
  - intensively (internship or retreat > five consecutive days) over the past 10 years,
  - more than 25 days of retreats (cumulatively) prior to the last 10 years;
- Not speaking English fluently.

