### **Objective 4 (WP 1 to 6)**

All cognitive measures, psychoaffective measures, life factors, blood, sleep and imaging measures at inclusion will be compared between the group of expert in meditation and the non-expert seniors. (see Section “*Descriptive analysis*” above for comparative methods)

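### Objective 4: the expert-versus-senior comparison on French verbal tests is open to confounding by native language, which the plan neither lists for collection nor handles

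*Combined protocol and SAP*

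**What the plan says.** Protocol section 4.2.1 places two language criteria under the non-expert seniors only: "Be a native French speaker" and "Not fluent in English (assessed by asking the participant". Both SAPs make the same split, with "French mother tongue" listed only for participants without meditation practice. The expert criteria start with "At least 10,000 hours of formal meditation practice in a lifetime, including at least 6 months in retreat" and go on to daily practice and type of practice. None concerns language.

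Section 4.3 states: "The meditating experts will be recruited in France and abroad". Table 7 gives the experts' recruitment area as Europe; the seniors come from the Caen area.

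For Objective 4 the secondary SAP plans that "All cognitive measures, psychoaffective measures, life factors, blood, sleep and imaging measures at inclusion will be compared" between experts and seniors. In Table 5 both groups take, at V1, the California Verbal Learning Test (CVLT), logical memory, autobiographical fluency, letter fluency (P) and category fluency (animals).

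On adjustment, protocol section 11.3.6 leaves the confounders to be identified for each analysis and gives age, education and gender as examples. The imaging section of the secondary SAP names age, MMSE, sex and education, with AD risk, cardiovascular risk and neuroticism as possible additions. Language appears in neither. The demographics listed for V0 (section 10.1.1.1) are age, gender, education and occupation.

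One criterion for all participants bears on this: "Present normal neuropsychological performance (based on age, gender, and education level) on the diagnostic battery tests (Table 4, Section 6.4". Table 4 includes the RL-RI16 verbal memory test, with a required z-score above -1.65, and an English test with an expected score below 16/18.

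**The concern.** Objective 4 is not randomised, so any characteristic fixed in one group and free in the other can produce a difference by itself. Native language is fixed in the seniors and free in the experts, and the verbal tests are given in French. A person tested in a second language may score lower on list learning, story recall or timed fluency for reasons unrelated to meditation. A lower expert mean could then hide a real advantage, or appear as a deficit that meditation did not cause. Composite scores that average such tests carry the same shift. Under the secondary SAP each such endpoint is tested at two-sided 5%, so no multiplicity correction would dampen a spurious result.

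**Working it through.** **1. Reproduce the plan's own figure.** Protocol section 11.2 compares 30 experts with 126 seniors at two-sided 5%. The standard error in SD units is sqrt(1/30 + 1/126) = 0.203. A two-sided t test with 154 df, using the noncentral t distribution, gives:

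| Effect size | Noncentrality | Power computed | Power stated |
|---|---|---|---|
| 0.74 | 0.74/0.203 = 3.64 | 95.2% | 95% |
| 0.67 | 3.30 | 90.6% | 90% |
| 0.58 | 2.86 | 81.0% | 80% |

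The stated figures reproduce.

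**2. Size of the bias.** Let p be the share of non-native experts and δ their deficit on a verbal test in SD units. The share among seniors is zero by criterion. With no true effect of expertise, the expected expert-minus-senior difference is -pδ. The documents give neither p nor δ. Assumed ranges: p from 10 to 40%, δ from 0.5 to 0.8 SD.

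**3. False-positive rate.** This is the probability of rejecting when pδ is the only difference. With the 150 seniors now planned, the standard error is sqrt(1/30 + 1/150) = 0.200, with 178 df:

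| p | δ | Bias (SD) | Noncentrality | Rate, 150 seniors | Rate, 126 seniors |
|---|---|---|---|---|---|
| 10% | 0.5 | 0.05 | 0.25 | 5.7% | 5.7% |
| 20% | 0.8 | 0.16 | 0.80 | 12.5% | 12.3% |
| 40% | 0.8 | 0.32 | 1.60 | 35.6% | 34.7% |

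**4. Masking.** As an illustration, take a true expert advantage of 0.74 SD on a verbal test (the protocol gives that figure for imaging). A bias of 0.16 SD against it leaves 0.74 - 0.16 = 0.58, and power falls from 95.2% to 81.0% (126 seniors).

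**5. Would adding a covariate solve it?** Put group and a native-language indicator into a linear model. The indicator is the same for every senior, so it is estimated from the experts alone. The group coefficient then becomes the difference between native-French experts and seniors. Adjustment therefore comes down to restriction, and stating the restriction openly is clearer.

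**6. Price of restriction.** Detectable difference at 80% power against 150 seniors: 0.56 SD with 30 experts, 0.67 SD with 20. Power at 0.74 SD against 126 seniors, if 10, 20, 30 or 50% of experts are set aside (27, 24, 21 or 15 left): 93.4%, 91.0%, 87.7% or 76.7%.

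**The case against.** The best case for the plan has four parts.

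- **The share may be small.** Recruitment includes France, none of the centres listed in section 4.3 is identified as lying outside it, and every participant must belong to a social security regime. This stands: the lower end of the range is negligible.
- **Experts pass the same screen.** RL-RI16 at z above -1.65 excludes clearly poor verbal memory in French. This also stands, but only as a limit. A cut-off at -1.65 leaves room for a mean shift of a few tenths of an SD among those who pass, and it does not test fluency.
- **The adjustment list is open.** Language could be added under section 11.3.6. That is permitted, but it is not prespecified, the variable is not listed for collection, and step 5 shows that regression cannot separate it from group without falling back on native-French experts.
- **Objective 4 is exploratory.** The protocol lists it among its more exploratory aims and frames it as an association. That lowers the priority of the point but does not answer it.

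A reader might go further and infer that the imaging comparison is confounded too, since the rationale says that "foreign language learning is known to have a positive impact on cognitive functions and brain" structures benefit. The documents do not support that step. The sentence concerns learning a language as active training, not fluency already held. Seniors are barred only from fluency in English, not from other languages. The Table 4 English limit, read literally, may cap experts as well. For similar reasons the English test score is a poor covariate: if the limit does not bind experts, the fluent ones have no comparable seniors, and the score says nothing about other languages.

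**Conclusion.** The concern holds for the French-language verbal tests in Objective 4 and for composites containing them. It holds as a risk, not as a demonstrated bias: the comparison is open to confounding, and to say that it is confounded would need a share of non-native experts that the documents do not give. On the assumed ranges, the false-positive rate per affected test lies between about 6% and 36%, so the problem could be trivial or serious. These figures make no allowance for the RL-RI16 screen, which would reduce them by an unknown amount. The imaging, blood, sleep and non-verbal comparisons are not shown to be affected. Objectives 1 and 1bis are randomised comparisons among seniors and are untouched.

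A separate ambiguity needs settling. The all-participants criterion refers to the Table 4 battery, Table 4 carries the English limit with no restriction to seniors, and the non-fluency criterion is written for seniors only. The documents do not say whether the English limit applies to experts.

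**What to change.** 1. Record each expert's native language.
2. In the secondary SAP, under Objective 4, list the language-dependent tests: CVLT, logical memory, and letter, category and autobiographical fluency. Prespecify that these, and any composite containing them, are analysed in native-French experts, at minimum as a sensitivity analysis reported beside the all-expert result.
3. Keep all 30 experts for imaging, blood, sleep and non-verbal measures.
4. Reconcile protocol section 4.2.1 with Table 4 on whether the English limit applies to experts.

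The cost is one item of data for at most 30 people, a few lines of SAP text, and precision on the verbal tests. If 20 experts remain, the detectable difference rises from 0.56 to 0.67 SD. If nearly all experts turn out to be native French speakers, almost nothing is lost and the question is closed.
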